## Discussion

The proposed study will be the first to examine the effects of CBD in early psychosis in a randomized control trial. It is hypothesized that CBD will improve symptoms, neurocognition, markers of stress and inflammation, eating behaviors, and neurophysiological measures. Importantly, moderators and mediators of the CBD effects will be explored. Potential moderators of response include baseline symptom severity, neurocognitive deficits, cortisol, and inflammatory biomarkers. We will explore improvements in inflammatory biomarkers as mediators of improvement in clinical symptoms, neurocognition, and metabolic profile. If a reduction in inflammatory measures mediates improvement in outcome, this would suggest that individuals with evidence of inflammation would benefit most from the proposed interventions. Finally, this will be the first human study to explore the effects of CBD on neurophysiological markers such as PPI and to examine whether a change in either MMN or PPI is a predictor of response to CBD in other domains. A better understanding of which early psychosis individuals are more likely to respond to CBD can inform treatment planning, specifying treatment for a particular individual based on presenting complaints or biomarker profile. A better understanding of which individuals are more likely to respond to CBD can inform treatment planning and personalize treatment.

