## Design and methods

### Aims of the study

The specific aims of this project are to determine if CBD augmentation compared to placebo: significantly modulates psychotic symptoms, cognitive symptoms, pro-inflammatory, and neurohormone biomarker levels, appetite and eating behavior, metabolic measures, and lastly changes neurophysiological abnormalities.

It is hypothesized that CBD will reduce symptoms, improve neurocognition, reduce markers of inflammation, reduce harmful eating behaviors, and improve information processing. Importantly, predictors, moderators, and mediators of the CBD effects will be examined. A better understanding of the mechanism by which CBD acts in early psychosis and the identification of which individuals are more likely to respond to CBD can inform treatment development and personalize treatment.

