As outlined in the study design (Fig. 1) and SPIRIT (Fig. 2), the trial will include 120 patients in the early stages of psychosis who will be randomly assigned in a 1:1 ratio to receive 1000 mg of cannabidiol or matching placebo as an add-on to current treatment to in a 8-week double-blind superiority randomized controlled trial to be performed over 3 years. The unblinded study statistician has created a list of participant identification numbers with randomized treatment assignments using the SPSS software prior to the start of the study subject recruitment. Blocked randomization will be used with a random block size (4 or 6). Subjects will be randomized to the study treatment group in a 1:1 ratio. No stratification method will be used. A research associate on the team who is not part of the study will be provided with that subject’s randomization code. Any violations of the inclusion and exclusion criteria, reasons for randomization failure including major protocol deviation, lost to follow-up, voluntary withdrawal, and study termination, will be communicated to the study statistician. This research associate is also the only person who is not blinded and who has access to the list that identifies the unique numbers on the relabeled bottles of the two products. They are then responsible for assigning the bottles to the patient. All clinical staff and participants involved in the study will be blinded with the sole exception of the independent statistician. The design is sufficiently powered to answer questions about the efficacy of CBD as an augmentation to antipsychotics in EP, predictors, mediators, and moderators of treatment response and further our understanding of the mechanism of action of CBD in early psychosis. Symptoms, eating behaviors, metabolic parameters, and hormonal and neuroimmune marker levels will be evaluated at baseline, 3 weeks, and 8 weeks, and neurocognitive and neurophysiologic assessment will be performed at baseline and 7 weeks. We will work closely with the UCSD Center for Medicinal Cannabis which has performed multiple CBD trials. UCSD IRB approval, FDA IND approval, and ClinicalTrials.gov registration are in place. Data will be deidentified and stored in RedCAP, a secure dataset available through UCSD. A data monitoring committee is made up of members of both funding agencies, which has assisted in the development of the database and ensuring compatibility with data forms. There is a Data and Safety Monitoring Board (DSMB) that reviews the progress of the study, recruitment, dropouts, and adverse events of trial participants on an annual basis, the board is made up of an independent group of investigators. Any protocol modifications will be reported to IRB, trial registry, and DSMB.

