#### Neurophysiological methods

Neurophysiological markers can provide corroborative data for treatment-related changes in underlying brain chemistry and associated changes in clinical symptoms of psychosis. The following evaluations will be conducted at baseline and at the end of the study.

In the startle prepulse inhibition (PPI) paradigm [103], electrodes (Ag/AgCl) are placed below and at the outer canthus of each eye. A customized startle-stimulus generating program (Grace Design Model m902 Amplifier and Neurobehavioral Systems Presentation software) will be used. The startle stimuli will be presented binaurally through headphones (TDH-39P) and include 70 dB [A] broadband background noise with a pulse (115 dB [A], 40-ms noise burst) presented either alone or following (30, 60, or 120 ms) a prepulse (86 dB [A], 20-ms noise burst). EMG activity will be analyzed using Brain Vision Analyzer (Cortech Solutions, Wilmington, NC) and high-pass filtered at 28 Hz at 12 dB/Oct. The waveform is then smoothed using a 40-Hz 24 dB/Oct low-pass filter. The magnitude of the peak startle response (highest point between 30 and 100 ms) is determined. Subjects with a relative lack of startle-elicited eye blink are excluded. The outcome is PPI or the percentage of change in startle magnitude to prepulse + pulse versus pulse-alone trials.

Stimulation, recording, and analysis techniques for calculating MMN amplitude will follow established methods [104, 105]. Participants will be presented with binaural tones (1 kHz computer-generated square wave stimuli, 85 dB[A] SPL, 1 ms rise/fall) with a fixed stimulus onset-to-onset asynchrony of 500 ms. Standard (*P* = 0.90; 50 ms duration) and deviant (*P* = 0.10; 100 ms duration) tones will be presented to participants in pseudorandom order while they watch a silent video. MMN waveforms will be generated by subtracting event-related potential (ERP) waveforms in response to standard tones from the ERPs generated in response to the deviant tones. The MMN amplitude will be measured as the mean voltage from 135 to 205 ms. The primary dependent measure is MMN amplitude at electrode Fz.

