Data will be analyzed using a mixed model [109] for all clinical, neurocognitive, biomarker, eating behavior, and electrophysiological markers. This method allows the inclusion of subjects with missing data or those who were terminated early in the study, without relying on data imputation procedures. This method provides an estimate of the individual variability around the population trend, the variability of the individual intercepts (baseline values) and slopes (changes across time), and the correlation between them. The model will include a random intercept, a random effect for assessment time, and fixed effects for comparison groups and group-by-time interaction. A fully saturated treatment-by-time model will be utilized for inference. Co-variance structure will be chosen based on Akaikes Information Criterion (AIC). Random group-level treatment effects will also be evaluated for importance based on the model AIC. Any group-level effects to be incorporated into the model. Denominator degree’s of freedom will be calculated using the Kenward-Roger small sample correction. Data will be analyzed from all randomized subjects on whom we have a baseline assessment and at least one post-baseline evaluation. Hypothesis 5 will be testing using the multiple regression procedure. All tests will be done using the SPSS version 24.

We will explore predictors (moderators) of treatment response including baseline symptom severity, neurocognition, biomarker (cortisol and inflammatory markers), and neurophysiological markers by building hierarchical linear models (HLM). The independent variables are the treatment group, moderator, and the treatment × moderator interaction. Mediation analyses will use a similar linear mixed models approach. Two conditions must be met: (1) correlation between the mediator and treatment and (2) relationship between the mediator and outcome. First, we will test the effect of the treatment group and the group × time interaction on the mediator, and we expect a statistically significant group × time interaction. Second, we will test the effects of mediator by group interaction on the outcome in the model that includes group and time; we expect a statistically significant mediator × time or mediator × group × time interaction.

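### Two sentences in the Discussion infer who will respond to CBD from results that cannot show it: a late change in MMN or PPI, and a mediated effect of inflammation

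*Protocol article*

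**What the plan says.** The article gives the trial a practical purpose beyond the average effect. Under Aims of the study it says that "the identification of which individuals are more likely to respond to CBD can inform treatment development and personalize treatment". The Discussion returns to this purpose and makes two statements about how it might be served.

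- On inflammation: "If a reduction in inflammatory measures mediates improvement in outcome, this would suggest that individuals with evidence of inflammation would benefit most" from the interventions.
- On neurophysiology, the trial will "examine whether a change in either MMN or PPI is a predictor of response to CBD in other domains".

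The measurement schedule is under Overall design: "neurocognitive and neurophysiologic assessment will be performed at baseline and 7 weeks", while symptoms and the inflammatory and hormonal markers "will be evaluated at baseline, 3 weeks, and 8 weeks". The section Neurophysiological methods says of MMN and PPI: "The following evaluations will be conducted at baseline and at the end of the study". Neither section schedules an early on-treatment reading of MMN or PPI.

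The Data analysis section plans moderation and mediation separately. For moderation: "We will explore predictors (moderators) of treatment response including baseline symptom severity, neurocognition, biomarker (cortisol and inflammatory markers), and neurophysiological markers", with the model given as "The independent variables are the treatment group, moderator, and the treatment × moderator interaction". For mediation it sets two conditions: treatment must affect the mediator, and the mediator must be related to the outcome.

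**The concern.** Identifying likely responders means finding something known before treatment that separates patients who gain more from CBD than from placebo from those who do not. Neither Discussion sentence describes such a finding.

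A change in MMN or PPI is itself a possible effect of treatment, and the article hypothesises that CBD improves information processing. It becomes known when treatment is nearly or fully over. A patient who improves for any reason may change on both the marker and the outcome, so an association between the two changes need not say anything about CBD.

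The inflammation sentence draws effect modification from mediation. Mediation describes the path by which an effect arises. Whether the effect differs by starting level is a separate question with its own test.

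At stake is a statement about whom to treat. Read as the Discussion has it, either result could be reported as support for personalised treatment when benefit does not vary between patients at all.

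**Working it through.** The article gives no figure on this point, so there is none to reproduce. The check is a reading of the schedule, a short piece of algebra and two illustrative simulations with assumed parameters.

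**1. Timing of MMN/PPI change.**

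| Measure | Assessed at |
|---|---|
| MMN, PPI | baseline, week 7 (Overall design); baseline, end of study (Neurophysiological methods) |
| Neurocognition | baseline, week 7 |
| Symptoms | baseline, week 3, week 8 |

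Taking week 7, the change is known at the same visit as the neurocognitive outcome and 8 − 7 = 1 week before the last symptom rating. Taking end of study, there is no lead at all. On either statement the change cannot guide a decision to start treatment.

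**2. Change against change when the drug does nothing.** Assumptions: 60 per arm less 20% dropout = 48 completers per arm, 96 in total; no treatment effect on anything; marker change and outcome change share a cause, giving a correlation of 0.3; 2,000 runs; tests at two-sided 5%.

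- Association in the CBD arm alone: significant in 56% of runs.
- Slope on marker change in the placebo arm, from the model with treatment, change and their product: significant in 55.5%.
- Treatment × change interaction: significant in 5%.

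The association thus appears equally often under placebo, and nothing in it is specific to CBD. The interaction keeps its nominal rate here. It would still not identify responders in advance, because the change is measured after randomisation.

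The within-arm rate can be checked by Fisher's z: the rate is about Φ(atanh(ρ) × √(48 − 3) − z), with z = 1.96 at 5% and 2.576 at 1%. For ρ = 0.3, atanh(0.3) × √45 = 0.3095 × 6.708 = 2.076. This gives Φ(0.116) = 0.55 at 5% and Φ(−0.500) = 0.31 at 1%.

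| Assumed ρ | 5% test | 1% test |
|---|---|---|
| 0.2 | 27% | 11% |
| 0.3 | 55% | 31% |
| 0.4 | 81% | 60% |

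These rates hold only for a test within the CBD arm, which the article does not specify, and for correlations that are assumed.

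**3. Mediation without effect modification.** Let T be treatment (0 or 1), ΔM the marker change and ΔY the outcome change:

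ΔM = a·T + error, ΔY = b·ΔM + error.

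The whole effect of T on ΔY is a × b. The baseline marker does not appear, so benefit is the same at every starting level although mediation is complete. Benefit varies with baseline only if a or b does, and neither mediation condition tests that.

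The simulation used a = −0.8 and b = 0.6, so the effect is −0.8 × 0.6 = −0.48 for every patient, with 96 completers and 2,000 runs:

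- Both mediation conditions met at 5%: 97.5% of runs.
- Treatment × baseline-marker interaction significant at 5%: 4.6%, about the nominal rate.

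The simulation applies the two conditions to change scores rather than through the planned mixed model. The algebraic point does not depend on that simplification.

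**The case against.** The strongest reply is that the plan already contains the right analysis. The Data analysis section specifies treatment × moderator models, and its list covers inflammatory and neurophysiological markers. The natural reading is that the word baseline governs the whole list. The Discussion also names cortisol and inflammatory biomarkers as possible moderators, separately from mediators. This stands. A reader might infer that the search for responders rests wholly on MMN/PPI change and on mediation; the documents do not support that.

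Second, no section says that the MMN/PPI analysis will be a correlation within the CBD arm at 5%. If change were handled as a mediator, the plan would first ask for a treatment effect on it, which would seldom appear with an inactive drug. The only significance level stated is the 1% of the power statement. This also stands. A reader might take the rates in the table as the trial's false-positive rate, but they are conditional illustrations only.

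Third, the neurophysiology serves a mechanistic aim, the analyses are described as exploratory and the inflammation sentence is hedged. That limits the consequence but does not make the inferences valid. The Discussion's list of potential moderators omits MMN and PPI, so the only predictive role it gives them is through their change. Its inflammation sentence is not linked to the interaction test planned elsewhere.

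One could add that patients with raised inflammation have more room for the marker to fall. That is a reasonable hypothesis, and it is the one the treatment × baseline interaction tests. Mediation does not establish it.

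**Conclusion.** The point holds, limited to the two Discussion sentences.

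The inflammation sentence draws a conclusion that does not follow: complete mediation is compatible with equal benefit at every baseline level. The MMN/PPI sentence gives the name of predictor to a post-randomisation measure available only at week 7 or end of study. It cannot identify likely responders before treatment, and its within-arm association with improvement could be ordinary co-variation.

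Both conclusions rest on the stated schedule and on the definitions of mediation and effect modification. The simulated percentages illustrate them under assumed parameters and are not estimates for this trial.

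The consequence is a possible unsupported statement about whom to treat, in exploratory analyses. A reader might infer that the efficacy result is also in doubt. Nothing here touches the primary analysis, the sample size or the data to be collected.

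**What to change.** Change the two sentences in the Discussion and clarify one in Data analysis.

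1. **Inflammation.** State that a mediation result will be reported as evidence on mechanism, and that whether patients with inflammation benefit more will be judged only from the treatment × baseline-inflammation interaction already planned.
2. **MMN and PPI.** Name baseline MMN and baseline PPI as moderators, tested in the planned treatment × moderator models. Describe change in MMN or PPI as a concurrent correlate or candidate mediator, report its association with outcome change in both arms, and attach no responder claim to it.
3. **Data analysis.** Make explicit that every listed moderator, including the neurophysiological markers, is its baseline value.

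The cost is wording only: no new visits, measurements or types of model. The downside is that any claim about responders becomes more cautious, and an inconclusive interaction would have to be reported as inconclusive even if mediation is shown.

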## Trial status

This trial is under IRB Project #200,789, version 17 of the University of California, San Diego Human Research Protections Program. Recruitment began on March 15, 2022, with an expected end date of October 1, 2024.

## Data Availability

The final access to the trial dataset will be available to funding agencies. In addition to the CARE team members who are involved in the data collection and analysis, the trial dataset will be shared with the CMCR and the Krupp Center of Integrative Research. Data collected for this study will be analyzed and stored at the CMCR. The de-identified, archived data may be used by other researchers including those outside of the study upon approval by CMCR and with appropriate regulatory approval. Data and results will be sent for publication on trial and manuscript completion. The consent material is included as supplementary information.

## Abbreviations

AE: Adverse event
AIC: Akaikes Information Criterion
APS: Attenuated psychosis syndrome
BDNF: Brain-derived neurotrophic factor
CARE: Cognitive Assessment and Risk Evaluation
CBD: Cannabidiol
cGMP: Good Manufacturing Practice
ECB: Endocannabinoid
ERP: Event-related potential
HPA: Hypothalamic-pituitary-adrenal
MCCB: MATRICS Consensus Cognitive Battery
MMN: Mismatch negativity
PANSS: Positive and Negative Syndrome Scale
PFC: Prefrontal cortex
PPI: Prepulse inhibition
SAFTEE: Systematic Assessment for Treatment Emergent Events
SCID-I: Structured Clinical Interview for DSM-V
THC: Tetrahydrocannabinol
UCSD: University of California, San Diego
